##### Primary Analyses of Intervention Effects

The primary hypothesis is that CHTC retesting will be associated with significant reductions in sexual HIV TRB (primary) outcomes compared to individual HIV testing. Using procedures similar to our previously published studies [54], outcome analyses will be conducted in a multilevel modeling framework. Analyses will use full-information maximum likelihood estimation and specify a negative binomial distribution consistent with the count nature of primary outcomes. The appropriateness of a Poisson distribution will be determined by inspection of the significance of the dispersion parameter in negative binomial models. This accounts for the nesting of individuals within couple. Because randomization occurs at the couple level, condition is a level 2 variable. The effect of the intervention will be evaluated by examining the regression coefficient (and associated *P* value). Separate models will be calculated to predict outcomes at 3- and 6-month follow-ups (with Bonferroni correction for repeated nonorthogonal tests). Mplus (Muthén and Muthén) accommodates count and dichotomous outcomes within the multilevel modeling context. Analysis of secondary outcomes will follow analogous analytic procedures.

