### Primary Outcomes

Primary analyses focus on 2 (individual-level) behavioral indicators of HIV transmission risk: (1) the number of CAS acts with a casual partner in the absence of the respondent taking PrEP and (2) CAS with a serodiscordant main partner who is not virally suppressed or concurrent CAS between main and casual partners in the absence of the respondent taking PrEP. The availability of day-level data generated by the timeline followback (TLFB) assessment allows for an examination of event-driven PrEP dosing as well as overall day-level adherence. Self-reported sexual behavior will be corroborated with results from bacterial STI (gonorrhea and chlamydia) testing. In instances where these indicators of HIV TRB suggest CAS with a casual (or main) partner occurred but was not reported, we will use data from the objective indicator.

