### Sample Size

Power to detect significant between-group differences in primary outcomes was calculated using the PASS program (version 2022; NCSS, LLC). Analyses focused on power to detect a significant between-group difference at any 1 follow-up time point. Results from the tests for difference between 2 Poisson rates in a cluster randomized design module indicated the study had power of >0.80 to detect a 20% or greater reduction in the rate of CAS with casual partners. This estimate assumed a sample of 200 couples with equal allocation to condition, and models were tested with based rates of 2-4 instances of CAS with a casual partner among the control (individual HIV testing and counseling) condition. Results from the tests for 2 proportions in a cluster-randomized design suggested proposed study has power of >0.80 to detect a 22% reduction in the proportion of reporting main partner TRB, assuming a sample of 200 couples and a 70% base rate in the control condition.

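### The scale of primary outcome 2 is not fixed: it is powered as a proportion, but the only model named for the primary outcomes is a count model

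*Protocol article*

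**What the plan says.** Three sections of the Protocol article bear on the scale of primary outcome 2.

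- **Primary Outcomes.** Outcome 1 is plainly a count: "the number of CAS acts with a casual partner in the absence of the respondent taking PrEP". Outcome 2 is "CAS with a serodiscordant main partner who is not virally suppressed or concurrent CAS between main and casual partners", again without PrEP. It is a composite of two kinds of event, and the text says neither how many nor whether any.
- **Sample Size.** Outcome 1 is powered as a comparison of Poisson rates. Outcome 2 is powered by a two-proportion test for clustered data, and the claim is "power of >0.80 to detect a 22% reduction in the proportion of reporting main partner TRB". The inputs given are 200 couples and a control rate of 70%. This treats outcome 2 as yes/no for each man.
- **Primary Analyses of Intervention Effects.** The models will "specify a negative binomial distribution consistent with the count nature of primary outcomes". Poisson is to be considered according to the dispersion parameter. Neither outcome is exempted. Later in the paragraph the article notes that Mplus can handle both count and dichotomous outcomes in multilevel models, but it does not say which outcome is dichotomous or which binary model would be used.

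**The concern.** The three sections cannot all hold for outcome 2. If it is yes/no, the only distribution the article specifies is wrong for it. If it is a number of acts, the only power statement given for it concerns a different quantity.

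This is one of two primary outcomes. The proportion of men with any event and the mean number of events are different estimands, with different effect measures, tests and power. A Poisson or near-Poisson negative binomial likelihood gives a 0/1 variable with mean p a variance of p instead of p(1 − p). Standard errors taken from that likelihood are therefore too large, and the test rejects too rarely.

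**Working it through.** **Inputs from the article.** 200 couples; control proportion 0.70; reduction 22%; comparison at one follow-up at a time. Equal allocation is stated for outcome 1 and assumed here for outcome 2, giving 100 couples or 200 men per arm.

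**Inputs not in the article, so assumed.** Two-sided alpha 0.05; within-couple ICC 0.3, with a range where shown; both readings of 22%: relative (0.70 × 0.78 = 0.546) and absolute (0.70 − 0.22 = 0.48). With two men per couple the design effect is 1 + ICC.

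**Step 1. Reproduce the stated power as a proportion test.** Effective n per arm = 200/1.3 = 153.8. Power = Φ{[d − 1.96·√(2p̄(1 − p̄)/n)] / √([p1(1 − p1) + p2(1 − p2)]/n)}.

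- Relative: d = 0.154, p̄ = 0.623; Φ[(0.154 − 1.96 × 0.0553)/0.0546] = 0.799.
- Absolute: d = 0.22, p̄ = 0.59; Φ[(0.22 − 1.96 × 0.0561)/0.0547] = 0.978.

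| ICC | Relative | Absolute |
|---|---|---|
| 0 | 0.891 | 0.995 |
| 0.2 | 0.830 | 0.985 |
| 0.3 | 0.799 | 0.978 |
| 0.5 | 0.740 | 0.959 |
| 1 | 0.614 | 0.891 |

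Power above 0.80 is attainable: for ICC up to about 0.30 on the relative reading, and at every ICC on the absolute reading.

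**Step 2. Suppose outcome 2 is 0/1 but gets the count likelihood with model-based standard errors.** The effect is the log ratio. The model's SE is √(1/y1 + 1/y2), where y1 and y2 are the expected numbers of men with an event. The true SE is √{(1 + ICC)·[(1 − p1)/y1 + (1 − p2)/y2]}. Power ≈ Φ[(log ratio − 1.96·SE_model)/SE_true].

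- Relative: y = 140 and 109.2; log ratio 0.2485; SE_model 0.1277; SE_true 0.0905; power ≈ Φ(−0.02) = 0.49.
- Absolute: y = 140 and 96; log ratio 0.3773; SE_model 0.1325; SE_true 0.0991; power ≈ Φ(1.19) = 0.88.
- Null at 0.70: SE ratio = 1/√(0.3 × 1.3) = 1.60; actual type I error = 2[1 − Φ(1.96 × 1.60)] ≈ 0.002.

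Simulation (20,000 trials, beta-binomial pairs, ICC 0.3) agrees:

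| Reading of 22% | Clustered binary test | Count model, model-based SE |
|---|---|---|
| Relative | 0.80 | 0.49 |
| Absolute | 0.98 | 0.89 |
| Relative, alpha 0.025 | 0.71 | 0.34 |

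Simulated type I error under the count model was 0.0013 to 0.0016, against about 0.05 for the binary test. The alpha of 0.025 corresponds to a Bonferroni split over the two follow-ups.

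**Step 3. Would a couple random effect change this?** These figures use the formula above; the two-level model itself was not fitted. In a Poisson model a couple effect is informed by extra variance in couple totals. Here the variance of a total is 2 × 0.7 × 0.3 × 1.3 = 0.55, below the Poisson value of 1.4. The couple variance and the dispersion parameter would both be pushed to zero, which leaves the plain Poisson standard error.

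**Step 4. Same log-ratio estimate with couple-robust standard errors.** At ICC 0.3, relative reading: power 0.798, type I error 0.048. Nearly all of the loss in Step 2 disappears.

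**Step 5. Suppose outcome 2 is a count.** As an illustration, assume 70% of controls have at least one act, a 22% lower rate, ICC 0 and alpha 0.05. The variance of the log rate ratio is (1/μ1 + 1/μ2 + 2k)/200 for dispersion k, with μ1 set so that 30% of controls have zero acts.

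| Dispersion k | Control mean | Power |
|---|---|---|
| 0 (Poisson) | 1.204 | 0.72 |
| 1 | 2.333 | 0.53 |
| 2 | 5.056 | 0.38 |

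The dispersions are assumed. The table shows only that the proportion-based figure does not carry over to a rate comparison.

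**The case against.** The best defence is that a binary analysis was probably meant. The secondary outcomes are counts of use and a questionnaire score, so outcome 2 is the only evident candidate for the remark about dichotomous outcomes. The sample-size calculation already treats it as a proportion, and the article promises to check distributional assumptions. A condensed article may leave the link function to a fuller plan, and on the worst reading the error is conservative, so it creates no false claim of benefit.

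Much of this stands as a reading of intent. It does not remove the contradiction: the remark describes what the software can do, while the sentence that assigns a distribution covers the primary outcomes without exception. The complaint is not that a detail is absent, but that the stated distribution conflicts with the stated power basis.

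Four stronger readings are tempting, and the article does not support them:

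- **That the stated power is wrong.** It is attainable as a two-proportion calculation (Step 1).
- **That the trial will lose a large part of its power on this outcome.** That needs 0/1 data, a count likelihood, model-based standard errors and a relative 22% all together. The article does not say which standard errors will be used or which 22% is meant.
- **That 22% is relative.** Nothing says so, and at ICC 0.3 the relative reading gives 0.799, just short of the stated figure.
- **That the scale will be picked after seeing the data.** The text leaves the scale unsettled but gives no sign of such an intention, and a fuller plan may settle it.

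**Conclusion.** The inconsistency is real and concerns a primary outcome. The definition gives outcome 2 no scale, the power calculation treats it as yes/no, and the analysis section treats it as a count.

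The consequence depends on which was meant. For a yes/no outcome the named model is misspecified. Its cost runs from close to nothing with couple-robust standard errors to a fall in power from 0.80 to about 0.49 with model-based ones on the relative reading, or from 0.98 to 0.89 on the absolute reading. These sizes rest on an assumed ICC of 0.3 and two-sided alpha 0.05. For a count outcome, the trial has no applicable power statement for this endpoint.

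**What to change.** 1. In Primary Outcomes, define outcome 2 as any qualifying event, yes or no, in the 30-day timeline followback window. This matches the power calculation.
2. In the analysis section, restrict the negative binomial and Poisson sentences to outcome 1 among the primary outcomes.
3. Name a two-level binary model for outcome 2: logistic, or log-link with couple-robust standard errors if a risk ratio is wanted.
4. In Sample Size, state whether the 22% reduction is relative (to 54.6%) or absolute (to 48%). The authors must supply this from their own calculation.

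If a count is intended instead, keep the count model and replace the proportion-based power statement for outcome 2 with one for a rate comparison, giving the assumed control rate, dispersion and ICC.

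The cost is a few sentences. No change to data collection is needed, and the article already notes that the software supports dichotomous outcomes. The change should be fixed before outcome data are examined by arm.

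### The stated Bonferroni correction covers the two visits but not the two primary outcomes, and the separate 6-month model leaves the 3-month data of dropouts unused

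*Protocol article*

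**What the plan says.** The Primary Outcomes section of the Protocol article states: "Primary analyses focus on 2 (individual-level) behavioral indicators of HIV transmission risk". Both are measured at 3 and 6 months after randomization. Under Primary Analyses of Intervention Effects the plan is a multilevel model with a negative binomial distribution. On estimation it says "Analyses will use full-information maximum likelihood estimation", and on clustering "This accounts for the nesting of individuals within couple"; repeated visits within a man are not mentioned as a level. On the visits it says "Separate models will be calculated to predict outcomes at 3- and 6-month follow-ups (with Bonferroni correction for repeated nonorthogonal tests". The test itself is described as "The effect of the intervention will be evaluated by examining the regression coefficient" with its P value.

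The Sample Size section says "Analyses focused on power to detect a significant between-group difference at any 1 follow-up time point". It reports power above 0.80 for each outcome and mentions no adjusted significance level.

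The article does not give the Bonferroni divisor, a primary visit, or a rule on whether one or both outcomes must succeed.

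**The concern.** Two outcomes at two visits make four primary tests. The only correction in the text is attached to the visit-specific models, and the word for repeated tests describes visits more naturally than different outcomes. Read that way, each outcome is held to 5% over its two visits and nothing holds the two outcomes together. If a positive result on either outcome counts as success, the chance of a false claim is close to double the nominal level.

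The second issue is the data that each model sees. When the 6-month outcome is the only dependent variable, a man seen at 3 months and lost by 6 months contributes no outcome of his own to that likelihood, although his 3-month value is informative. The attrition step under Data Screening Procedures and Analyses of Attrition does not recover it: it looks at demographics and at the 12-month 4Us assessment, not at the 3-month outcome. Attrition is foreseeable here, since the Retention Plan provides for couples who separate during the study.

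**Working it through.** **Inputs.** From the article: 2 primary outcomes, 2 visits, 200 couples allocated equally (so 200 men per arm), a control rate of 2 to 4 acts and a 20% reduction. Not stated, so assumed: two-sided alpha 0.05, Bonferroni divisor 2, success on either outcome, correlations between test statistics of 0 to 0.7, dropout between visits of 5-20%, and within-man correlation between visits of 0.3-0.7. The within-couple intraclass correlation (ICC) is also not stated.

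**The plan's own power figure.** It can be checked only for consistency, because alpha and the ICC are missing. For a control rate of 2 against 1.6 and ICC 0, the variance of the difference is (2 + 1.6)/200 = 0.018, so z = 0.4/√0.018 = 2.98.
- At two-sided 0.05: Φ(2.98 − 1.96) = 0.846, consistent with power above 0.80.
- At 0.025: Φ(2.98 − 2.24) = 0.770.
- At 0.0125: 0.686.

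A positive ICC lowers these figures. At a control rate of 4 and ICC 0 they are 0.988, 0.976 and 0.957. The claim above 0.80 at the low base rate therefore fits an unadjusted 0.05, not a Bonferroni-adjusted level.

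**Family-wise error.** Four tests at 0.05/2 = 0.025:
- Upper bound: 4 × 0.025 = 0.10.
- Independent tests: 1 − 0.975⁴ = 0.0963.
- Simulated correlated normal statistics, with r between visits and c between outcomes: 0.085 at r = c = 0.5, and 0.073 at r = c = 0.7.

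The range is about 0.07 to 0.10. With four tests at 0.05/4 = 0.0125, the bound is 0.05 and the value under independence is 1 − 0.9875⁴ = 0.0491.

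**Information lost at 6 months.** This is a normal approximation with dropout fraction q between the visits and correlation ρ. The single-visit variance is proportional to 1/(1 − q). The joint-model variance is proportional to (1 − ρ²)/(1 − q) + ρ². Ratio of single-visit to joint:

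| q | ρ = 0.3 | ρ = 0.5 | ρ = 0.7 |
|---|---|---|---|
| 0.05 | 1.005 | 1.013 | 1.025 |
| 0.10 | 1.009 | 1.026 | 1.052 |
| 0.20 | 1.018 | 1.053 | 1.109 |

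**Price of a stricter threshold.** A test with 80% power at 0.05 has z = 1.960 + 0.842 = 2.80. At one visit, power is 0.712 at 0.025 and 0.619 at 0.0125.

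**Testing each visit or the average.** These figures are for one outcome with between-visit correlation 0.5, z = 2.80 at the visit with the full effect, and error controlled over both outcomes:

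| Effect pattern | Either visit, 0.0125 per test | Visit average, 0.025 |
|---|---|---|
| Same at both visits | 0.78 | 0.84 |
| Halved at the other visit | 0.63 | 0.57 |
| One visit only | 0.63 | 0.27 |

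**The case against.** The strongest reply is that the wording does not exclude a divisor of 4, and that the family of tests may be set out in an analysis plan that is not shown. This stands in part. Misallocated alpha is not proven, and the 0.07 to 0.10 depends on the three assumptions above. If both outcomes had to succeed, no split across outcomes would be needed. What the article does say, however, ties the correction to the visits and leaves the outcomes without one.

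Separate visit models are also a legitimate choice that matches a power calculation made for one time point.

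A reader might infer four stronger things, and the documents support none of them:

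- *That the separate models defeat the full-information likelihood, or that a claimed missing-at-random protection fails.* The article makes no missing-at-random claim. The multilevel likelihood still uses couples with one partner observed, and predictors of attrition found among the demographic and 12-month variables enter the outcome models. Only dependence of dropout on the 3-month outcome is left uncovered.
- *That a joint model by itself controls the error rate.* It does not: two joint tests at 0.05 each reach 1 − 0.95² = 0.0975. The multiplicity procedure does that work, and separate models at 0.0125 would be equally valid.
- *That the plan loses power by splitting alpha over visits.* If a win at either visit counts, power for one outcome at 0.025 per visit is about 0.85 at correlation 0.5 with a constant effect. The visit-averaged test at 0.025 has 0.84.
- *That a visit average is always the better primary test.* It gains only under a sustained effect. The article's Introduction cites discrepant perceptions of the agreement in 22.6% of couples and broken agreements in 12.7% six months after couples testing, so fading cannot be ruled out.

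**Conclusion.** The point holds in two parts. First, as worded, the correction covers the repeated visits and leaves the two primary outcomes uncorrected. The family-wise error is then about 0.07 to 0.10, assuming two-sided 0.05, a divisor of 2 and success on either outcome. Second, the 6-month model does not use the 3-month outcome of men missing at 6 months. The loss of precision is modest (variance about 0.5% to 11% larger under the assumed dropout and correlation), with possible bias if 3-month behaviour predicts dropout. The size of that bias cannot be judged from the article. Both parts concern the primary tests and should be settled before the data are analysed.

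**What to change.** Fit one longitudinal model per outcome with the 3- and 6-month values together: participants within couples, and terms for visit, condition, condition by visit, and the baseline value. Take the 3- and 6-month condition effects from that model. Apply Holm over the four primary tests (2 outcomes × 2 visits), so that the ordered thresholds are 0.05/4 = 0.0125, 0.05/3 = 0.0167, 0.05/2 = 0.025 and 0.05. State the overall alpha and sidedness, and state power at the level actually used.

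An average effect over both visits, with Holm over the two outcomes, is an alternative only if the team expects a sustained effect and says so in advance. It changes the primary estimand and loses power if the effect fades or appears at one visit.

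The cost is some wording, a larger Mplus model, and per-test thresholds that start below 0.025. For a single visit, 80% power at 0.05 falls to about 62% at 0.0125, against 71% at 0.025; Holm recovers part of this once a first test is passed.

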##### Moderation or Mediation Analyses

Where possible, we will evaluate whether retesting using the adjunct (substance use calendar and ACT video) components is associated with specific reductions in primary (HIV TRB) outcomes. While the primary goal of this analysis is to test whether CHTC retesting, in general, is associated with benefits above and beyond individual HIV testing, the study design permits a preliminary examination of whether retesting that involves these adjunct components developed by our team is associated with additional benefits above and beyond retesting using the standard CHTC protocol. We will conduct a preliminary examination of this possibility using analytic procedures analogous to those used to evaluate effects on secondary drug use outcomes.

##### Data Monitoring

The DSMB, comprising 3 independent experts in the fields of HIV prevention, substance use intervention, and biostatistics, was convened in accordance with NIH policy to oversee the original 4Us trial (NCT05000866). The DSMB convenes at least annually in response to the occurrence of any serious adverse events.

Study staff will monitor the occurrence of 2 anticipated adverse events, including HIV incidence and IPV. Participants provide data on these at each follow-up, and responses are reported to the DSMB annually by the primary investigator. The primary investigator will report unanticipated events and those reported spontaneously by participants to the DSMB on an ongoing basis. These are also summarized in their annual meeting report.

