## Methods

### Trial Design

This study uses a randomized controlled trial design integrated with the ongoing 4Us trial [47]. The purpose of the original 4Us trial is to test the efficacy of 2 intervention components for CHTC: a communication skills training video and a substance use module. Couples are eligible for the original 4Us trial if at least 1 partner reports HIV negative or unknown serostatus, reports at least 1 drug, and engages in HIV TRB. Participants in this ongoing trial (4Us) complete an individual baseline assessment, after which couples complete a CHTC session following the standard CHTC protocol. In a full-factorial design, half of the couples are randomly assigned to complete an adjunct module addressing drug use, and half are assigned to view an assertive communication training (ACT) video (later referred to respectively as the substance use calendar and ACT video). This results in 4 study conditions (CHTC as usual, CHTC plus the substance use calendar, CHTC plus the ACT video, and CHTC plus both adjunct components). Follow-up assessments occur 3, 6, 9, and 12 months post intervention using procedures analogous to the baseline. Participants who complete the 12-month follow-up of the 4Us trial and meet eligibility criteria for the CHTC retesting trial are consented individually to participate in this protocol. If both couples consent into this protocol during their 12-month assessment, they are randomly assigned to either couples retesting or individual HIV testing. Those randomized to couples retesting complete the same 4Us condition they were assigned at baseline. Follow-ups are then completed 3 and 6 months later (15 and 18 months post completion of the baseline in the original 4Us trial).

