##### Trial Modification and Discontinuation

There are no plans to conduct interim analyses, and no a priori stopping rule has been established for this trial. Randomization may be discontinued, and the trial stopped under the guidance of the DSMB in response to adverse event review. Sponsor and DSMB approval are required for substantive changes to trial design. Changes also require institutional review board approval before implementation, and the clinicaltrials.gov record would be updated to reflect modifications.

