## Results

This study began recruitment in January 2023, and all participant components are projected to end in May 2025. As of December 2023, 102 individuals (51 couples) have enrolled in the CHTC retesting trial.

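### IPV and HIV infections disclosed at scheduled follow-ups go to the DSMB once a year, while unanticipated and volunteered events go by an ongoing route; the routing follows how an event is learned of, not its seriousness

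*Protocol article*

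**What the plan says.** Data Monitoring names the harms to be watched: "Study staff will monitor the occurrence of 2 anticipated adverse events, including HIV incidence and IPV". It then sets two reporting routes.

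- Answers given at scheduled assessments: "Participants provide data on these at each follow-up, and responses are reported to the DSMB annually by the primary investigator".
- Everything else: "The primary investigator will report unanticipated events and those reported spontaneously by participants to the DSMB on an ongoing basis".

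On meetings, the same section says: "The DSMB convenes at least annually in response to the occurrence of any serious adverse events".

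Trial Modification and Discontinuation then says: "There are no plans to conduct interim analyses, and no a priori stopping rule has been established for this trial". Stopping is left to the board's judgement: "Randomization may be discontinued, and the trial stopped under the guidance of the DSMB in response to adverse event review".

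Trial Design places the two follow-ups 3 and 6 months after the 12-month 4Us assessment at which couples are randomised. The Results section gives the calendar: "This study began recruitment in January 2023, and all participant components are projected to end in May 2025".

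**The concern.** The two harms that the trial expects, and asks every participant about, take the slower route when they are found by asking. IPV disclosed in answer to the 3-month question is neither unanticipated nor volunteered, so it falls under the annual sentence. On the natural reading, the same episode mentioned in a phone call would go by the ongoing route. No seriousness criterion decides between the two. The systematic collection, which covers both arms alike, is thus the slowest channel to the board.

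This matters because the trial has no interim analysis and no preset stopping rule. The only trial-level safeguard described is the board's review of adverse events, and that depends on what the board has been told. The retesting session also has a counsellor open a conversation between partners about sex outside the relationship. The Introduction recognises that some partners fear that raising changes of this kind could harm the relationship. If retesting did raise IPV, couples could go on being randomised while the elicited reports waited.

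**Working it through.** There is no plan figure to reproduce. The check is a comparison of the sentences, followed by calendar arithmetic.

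**Routing, read literally (Data Monitoring)**

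| How the event comes to light | Route to the DSMB |
|---|---|
| IPV or HIV, elicited at a follow-up | annual report |
| IPV or HIV, volunteered | ongoing, no time limit given (natural reading; not spelled out) |
| Unanticipated event | ongoing, no time limit given |
| Serious IPV or HIV event, elicited at a follow-up | no separate route stated |

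The meeting sentence runs a fixed minimum frequency together with an event trigger. Even if it is read as both, a board can convene only on an event that has reached it, and the last row gives no means for that before the annual report.

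**Calendar**

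1. Trial length, January 2023 to the end of May 2025: 2 × 12 + 5 = 29 months, or 29 / 12 = 2.4 annual intervals. About two annual reports fall while the trial is active.
2. Enrolment window, if the last couple still completes 6 months: 29 − 6 = 23 months.
3. Wait from an elicited answer to the next annual report: 0 to 12 months. If answers fall uniformly within the year (assumption), the mean is 12 / 2 = 6 months, and (12 − 6) / 12 = 50% wait longer than 6 months, a participant's whole follow-up.
4. Share of the enrolment window covered by the wait: mean 6 / 23 = 26%; maximum 12 / 23 = 52%.

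**Couples randomised during the wait**

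The Abstract gives 53 couples by February 2024, about 14 months: 53 / 14 = 3.8 a month. The Results section gives 51 couples by December 2023, about 12 months: 51 / 12 = 4.25 a month. Assume a constant pace, and equal allocation as in the Sample Size section.

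| Wait | Couples randomised | Of these, to retesting |
|---|---|---|
| 6 months (mean) | 23 to 26 | 11 to 13 |
| 12 months (maximum) | 45 to 51 | 23 to 26 |

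The constant pace is generous for the latest period: 53 − 51 = 2 couples were added between the two dates.

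**Worst case from event to board**

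An IPV event just after the session, first asked about at 3 months and disclosed just after an annual report, takes 3 + 12 = 15 months. This is an extreme, not a typical delay. It also suits IPV better than HIV, because the HIV Testing section schedules the follow-up HIV test at 6 months.

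**The case against.** The case for leaving the text alone has several parts.

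- **The board is not limited to one meeting a year.** Annual is a floor, and the same sentence links meetings to any serious adverse event without excluding anticipated or elicited ones. A reader might infer that the DSMB cannot convene on an elicited event, or cannot act in time. The document does not support that. The wait can be close to zero, and an earlier meeting is allowed for. What remains is that no stated route carries such an event to the board early.
- **The contrast between routes can be overdrawn.** A reader might infer that volunteered events are forwarded at once. The article sets no time limit for the ongoing route, and it does not say in terms that volunteered events include IPV and HIV. Both cautions stand.
- **The article is condensed.** Definitions of seriousness, expedited timelines and table layouts commonly sit in a monitoring plan or charter that is not shown. For that reason the absence of tables by condition, or separate from 4Us, is no finding. The annual route for elicited answers is different: it is stated, not omitted.
- **Individual protection does not run through the DSMB.** Under Posttrial Care, staff deliver positive HIV results and discuss linkage to care, and the laboratory reports to the state. This is correct, but it does not bear on whether randomisation continues.
- **The expected risk is modest.** The Background cites no evidence that CHTC increases IPV, Eligibility Criteria exclude IPV with ongoing safety concerns, and every couple has already had one CHTC session. This lowers the stakes. However, the Abstract says that the effects of retesting have not been studied, and the protocol itself chose these two events to monitor.

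**Conclusion.** The point holds as a problem of routing and of reconciling the article's own sentences. Elicited IPV and HIV events go to the DSMB annually, while unanticipated and volunteered events go by an ongoing route, and seriousness plays no part in the choice. The delay after disclosure is 0 to 12 months, about 6 on average under uniform timing, set against 6 months of follow-up per participant and about 29 months of trial. At the reported pace, an average wait corresponds to about 23 to 26 further couples randomised, half of them to retesting.

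This rests on three things: a literal reading of the annual sentence, the natural reading that volunteered events include IPV and HIV, and no unshown monitoring document that sets a faster route. It does not show that oversight fails, and it does not touch the validity of the efficacy comparison. It is a cheap improvement.

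**What to change.** Reconcile the Data Monitoring sentences with each other and with the stopping provision in Trial Modification and Discontinuation:

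1. Send IPV and new HIV infections elicited at follow-up, at minimum those that are serious, to the DSMB by the ongoing route already used for unanticipated and volunteered events.
2. Keep the annual report as the cumulative summary.
3. Reword the meeting sentence so that the board meets *at least annually, and additionally in response to any serious adverse event*.

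If a monitoring plan already provides this, the article's text need only be brought into line with it. The cost is a wording change and slightly more reporting work. No new data are collected, and the sample size and analysis are unchanged.
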